#### Cost-effectiveness evaluation

Primary outcome measure is costs per QALY. A cost-utility analysis will compare cost differences (incremental costs) with the difference in health effects measured in QALYs. In order to calculate costs, the volume of care will be linked to the actual, integrated cost prices per medical service [82]. Net costs per nursing day will be calculated as well as the costs for diagnostics and therapy with help from the manual of cost research in economic evaluations [83] and will be judged for usability according to recent DBC-information. Wrong bed days will be estimated according to the method of Van Straten [84]. The extra costs of a stay at the centre (e.g. training, availability specialist care doctors and nurses, mobilization, extra physiotherapy etc) in comparison with the usual geriatric care provided in the program will be measured, making a distinction between once-only costs and structural costs [85]. Integrated costs per day nursed at the centre will be calculated with aid of the activity base costing method [82]. Data on personnel, material costs, diet-related costs, accommodation and overheads will be accessed using centre registries and information systems, and extra information is collected through regular observation and self-registration of professional activities. Integrated costs per hour, per product cluster, will be used for home-care. For the remaining extramural care (general practitioner care, physiotherapy, social services etc.) costs will be assessed with information from cost manual and recent cost-price research. Costs are discounted at a constant discount rate of 4% per year. Future health effects are discounted at a constant discount ratio of 1.5% per year. Net savings could occur on balance during hospital care, whilst a stay at the reactivation centre as well as home care will lead to use of additional means. This valance of savings and extra costs cannot be indicated in advance. It is expected that continuity of care will possibly lead to considerable savings [86].

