**Health care volumes**					
Period hospital admission:	Hospital registries	Time of hospital discharge			+ during inclusion
*- amount of hospital days (days admitted)*	Hospital registries	Time of hospital discharge			
*- total days/time admitted at ICU*	Hospital registries	Time of hospital discharge			
*- amount of consults medical/paramedical*	Hospital registries	Time of hospital discharge			
*- amount of large scans and diagnostics*	Hospital registries	Time of hospital discharge			
*- amount of large treatments/operations*	Hospital registries	Time of hospital discharge			
*- wrong bed days*	Hospital registries	Time of hospital discharge			
*- amount of days admitted*	Hospital registries	Time of hospital discharge			
*- amount of consults medical/paramedical*	Hospital registries, interviews personnel	Time of hospital discharge			+ during inclusion
*- time/amount of multidisciplinary meetings*	Hospital registries, interviews personnel	Time of hospital discharge			+ during inclusion
Health care utilization patient in periods before and after hospital stay	Interview patient and mailed paper questionnaire primary caregiver	**X**	**X**	**X**	
*- homecare/nursing home/etc*					
Average time per consult	Interviews professionals (sample)	During inclusion period			
Amount informal care	MDS + questionnaire informal caregiver	**X**	**X**	**X**	Amount in hours
Amount (multidisciplinary) coordination	Interviews professionals				Amount in hours

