##### Quality of life (patient)

The EuroQol (EQ6D) is administered to measure quality of life among patients and their caregivers. It is part of the MDS and will be used to calculate cost-utilities of health care [53].

The Dutch version of the SF-20 is administered and aims to score 6 sub-dimensions such as physical functioning, social functioning and experienced health [54]. The SF-20 is chosen since it is quick to administer and many of its questions are already part of the MDS. The SF-20 has shown good test-retest reliability and acceptable convergent and discriminative validity for a group of elderly persons, even though some precaution is advised in using the questionnaire with elderly people living at home [55]. The short version of the Social Production Function Scale SPF-IL scale measures social well-being by means of the dimensions "affection", "behaviour confirmation" and "status" as well as physical well-being by means of the dimensions "comfort" and "stimulation" [56].

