#### Cost-effectiveness evaluation (table 5)

A cost-utility analysis will compare cost differences (incremental costs) of provided health care in the three hospitals with the difference in health effects measured in quality adjusted life years (QALYs). QALYs combine alterations in quantity and quality of life (mortality and morbidity) into a combined generic instrument. Data on quality of life will be measured by means of the EQ6D and SF20 for patients and by means of the EQ6D, CarerQoL and SF-20 for the primary informal caregiver (see effect evaluation). Cost information is gathered by means of hospital information systems, patient files and questionnaires for both patient and primary caregiver at baseline (T0), after three months (T1) and after 12 months (T2). A societal perspective is used; taking into account both direct and indirect costs within as well as outside health care. Data collection on utilization of care in hospital (nursing days, diagnostic and therapeutic activities and out-patient visits), nursing home (days), rehabilitation (admissions/outpatient), and home care (care hours according to product clusters) will take place centrally, according to a standard method, by means of standardized files and standard cost diaries as well as through patient and caregiver questionnaires

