#### Effect evaluation and process evaluation

##### Effects and process evaluation of the hospital based reactivation care program

Corrections will take place by means of 'analysis of covariance' for baseline differences in determinants between the locations that could explain differences in functioning or quality of life. Multiple regression analysis will be administered for various outcome variables such as linear regression for continuous outcomes; logistic regression for dichotomous outcomes; proportional odds regression for orderly outcomes and Cox proportional hazards regression for events that occur over time (such as death). Analysis of outcomes at three and twelve months will take into account dependency of these outcomes within persons. The degree of exposure to integrated, multidisciplinary care within the intervention location (process evaluation) will also be correlated with effect measurements in order to see whether greater exposure leads to greater effects. Regression analysis will trace sub-group effects and an interaction term will be included in the model, between type of hospital and sub group (e.g. elderly at high risk for functional loss in comparison to elderly at relatively lower risk for functional loss).

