### Weaknesses

This study is mainly a cohort study and not a randomised controlled trial (except for the evaluation of a stay at the centre for prevention and reactivation). Nevertheless a cohort study seems our best option for several reasons: Firstly, during hospital treatment, contamination of a control group would be inevitable within one hospital since the same personnel will be treating patients from different groups at the same departments [88]. Secondly, the new program will be the standard care provided in the intervention hospital thereby making randomisation within the hospital not possible. Furthermore, randomisation of treatments between hospitals is not possible since each hospital already has its own standard provided care. Thirdly, during the follow up period after hospital discharge people already have their own regular general practitioner (GP) whose practice is usually close to the patient's home and who is familiar with the patients health and history, making it unrealistic to randomize patients among GP's [88] or home care organizations as well as other first line practitioners. Finally, by conducting a prospective cohort study we aim to investigate health care as provided in a real life situation, thereby improving the generalisability of the study.

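### The cost-utility comparison of the three non-randomised hospitals states no baseline correction; the correction set for the effect outcomes may be read as reaching QALYs but does not reach costs

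*Protocol article*

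**What the plan says.** The economic comparison is described twice in the protocol article. Under Data collection, Cost-effectiveness evaluation (table 5), it reads "A cost-utility analysis will compare cost differences (incremental costs) of provided health care in the three hospitals with the difference in health effects", with those effects expressed in QALYs. Under Data analysis, Cost-effectiveness evaluation, the section opens with "Primary outcome measure is costs per QALY" and then repeats the comparison: "A cost-utility analysis will compare cost differences (incremental costs) with the difference in health effects measured in QALYs". That section goes on to fix cost-price sources, a method for wrong bed days, activity-based costing and discount rates of 4% and 1.5%. It names no covariate and no baseline correction.

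Baseline correction is stated elsewhere. For the hospital comparison, the section on effects and process evaluation of the reactivation care program says "Corrections will take place by means of 'analysis of covariance' for baseline differences in determinants between the locations", and limits these determinants to those that might account for differences in functioning or quality of life. The section on the centre for prevention and recovery plans adjustment for baseline characteristics in the nested trial.

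The hospital comparison is not randomised: the Weaknesses section says "This study is mainly a cohort study and not a randomised controlled trial", with the centre stay as the exception. On the data side, the EuroQol is collected at T0, T1 and T2 (Table 2), and of this instrument the article says "It is part of the MDS and will be used to calculate cost-utilities of health care". Table 5 lists "Health care utilization patient in periods before and after hospital stay", also at T0, T1 and T2.

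**The concern.** Patients in the three hospitals may differ at admission in health-related utility, case mix and care already in use. The article accepts this for the effect outcomes, since it plans a correction there. The economic section makes the same between-hospital contrast and is silent on it.

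If the cost and QALY differences are computed as the sentence reads, any difference present before treatment is credited to the programme or held against it. It can enter both parts of the ratio: the QALY difference through admission utility and prognosis, and the cost difference through care use that was already higher or lower before admission. The effect evaluation and the economic evaluation could then point in different directions on the same patients merely because only one was corrected.

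**Working it through.** **1. Where each quantity is corrected (hospital comparison).**

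| Quantity | Baseline correction stated? |
|---|---|
| Functioning | Yes, effect evaluation |
| Quality of life | Yes, effect evaluation |
| QALYs | Not named; arguably covered, because they are built from quality-of-life data |
| Costs | Not named; the stated criterion (determinants of functioning or quality of life) does not select cost determinants |

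Pre-admission care use is collected at T0, but no section assigns it as a covariate.

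**2. The plan's own figures.** The article gives no power or precision figure for costs or QALYs. Its only power figures are for Katz-15. With a two-sided alpha of 0.05 (assumed) they reproduce: 733 v 300 gives 95.4% at d = 0.25 (stated 95%) and 83.1% at d = 0.2 (stated 83%); 733 v 600 gives 95.3% at d = 0.2 (stated 95%). They are used below only for group sizes and for scale.

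**3. Weights of the three visits.** The article does not say how the QALY is built. Assume the usual area under the curve by straight lines, with visits at 0, 0.25 and 1 year:
- T0: 0.25/2 = 0.125
- T1: 0.25/2 + 0.75/2 = 0.50
- T2: 0.75/2 = 0.375

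**4. Spurious QALY difference with no treatment effect.** Let D be the difference between hospitals in T0 utility and b the carry-over slope from T0 to each follow-up value. Then

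spurious difference = D × (0.125 + 0.875 × b).

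Both D and b are assumptions.

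| D | b = 0.3 | b = 0.5 | b = 0.7 | direct T0 part (0.125 × D) |
|---|---|---|---|---|
| 0.02 | 0.0078 | 0.0112 | 0.0147 | 0.0025 |
| 0.05 | 0.0194 | 0.0281 | 0.0369 | 0.00625 |
| 0.10 | 0.0388 | 0.0563 | 0.0737 | 0.0125 |

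For D = 0.05 the direct part is 0.00625/0.0369 = 17% to 0.00625/0.0194 = 32% of the total. The rest is carry-over, which is ordinary confounding by baseline.

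**5. Scale.** Suppose a true effect of 0.2 SD at both follow-ups and an assumed EuroQol SD of 0.20 to 0.30. It is worth 0.2 × 0.20 × 0.875 = 0.035 to 0.2 × 0.30 × 0.875 = 0.0525 QALY. Against that, D = 0.05 gives an artefact of 0.0194/0.0525 = 37% to 0.0369/0.035 = 105%; D = 0.02 gives 0.0078/0.0525 = 15% to 0.0147/0.035 = 42%. The 0.2 is borrowed from the Katz-15 calculation, so this shows order of magnitude only.

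**6. Simulation, true effect zero** (SD 0.25, b = 0.5, 733 v 300, 2,000 runs per row).

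| D | unadjusted mean | rejected, unadjusted | adjusted for T0 utility, mean | rejected, adjusted |
|---|---|---|---|---|
| 0.02 | 0.011 | 15% | 0.000 | 5% |
| 0.05 | 0.028 | 55% | 0.000 | 5% |
| 0.10 | 0.056 | 99% | 0.000 | 5% |

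The simulation has no deaths, no missing data and no confounder other than T0 utility, and T1 and T2 are independent given T0. The adjusted model is therefore correct by construction. A closer T1–T2 link would lower the unadjusted rejection rates but leave the bias unchanged.

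**7. Costs.** By the same logic, a difference in pre-admission care costs that carries over with slope c adds c times that difference to incremental costs. The article gives no cost figures, so no size can be put on this.

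**The case against.** The strongest reply is that the text is silent rather than wrong. The sentence quoted is the standard definition of an incremental analysis: it says what is compared, not how it is estimated, and it rules out no covariate. This is a condensed article, and a regression model for costs and QALYs may stand in the full plan. That much holds. A reader might infer that the sponsor chose unadjusted differences, or decided not to use prior care use as a covariate; the article says neither.

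The quality-of-life wording of the effect-evaluation correction can also fairly be read as extending to QALYs. It cannot be stretched to costs in the same way.

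The Setting section says the hospitals were chosen for similar case mix, and no imbalance is shown. True, but that statement comes without figures, and the article itself plans a correction for differences between locations.

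Further limits also stand. The area-under-the-curve construction, D, b and the SD are all assumed, and direct entry of the T0 value is the minor part. One might take costs per QALY as the primary outcome of the whole study, but the label appears only under the economic evaluation, cost-effectiveness is the last of four objectives, and the power calculation rests on Katz-15. Finally, the point should not be carried over to the nested trial: its arms are randomised, and baseline adjustment is already planned there.

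What the reply does not remove is the contrast within the article. Confounding control is stated for the effect outcomes, and the economic section is detailed on prices and discounting, yet the step that makes a non-randomised cost comparison interpretable is missing there.

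**Conclusion.** The point holds in a limited form. For the hospital comparison, the economic section states no baseline correction. The correction given for the effect outcomes may reach QALYs but does not reach costs. Followed as written, pre-treatment differences enter costs per QALY.

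On the QALY side, the size is D × (0.125 + 0.875b): 0.019 to 0.037 QALY for D = 0.05 and b = 0.3 to 0.7, and 0.008 to 0.015 for D = 0.02. This rests on an assumed area-under-the-curve QALY and assumed D and b. On the cost side no size can be given.

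A reader might conclude that the cost per QALY will be biased or will change sign. The documents do not support that: no baseline difference is shown, and the artefact matches or exceeds the reference effect only at the extreme of the assumed ranges. This is an improvement available at almost no cost, not a demonstrated error in a result.

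**What to change.** In the Data analysis section on cost-effectiveness, state that the baseline correction planned for the effect evaluation also applies to the economic comparison between hospitals:

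- incremental QALYs adjusted for T0 EuroQol utility and the baseline determinants used in the effect evaluation;
- incremental costs adjusted for pre-admission care use recorded at T0 and the same determinants;
- costs per QALY formed from the two adjusted differences;
- unadjusted differences reported as supporting results.

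The same section should say how the QALY is computed from T0, T1 and T2. The choice of joint estimation method can be left to the analysis plan.

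The cost is a few sentences of text and a little analysis work. T0 utility and care use are already collected, and the other determinants are those already planned for the effect evaluation, so no patients, visits or measurements are added. Adjustment removes only differences in what was measured; other differences between hospitals remain a limitation of the design.

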## Discussion

The aim of this evaluation study is to compare outcomes, processes and cost effectiveness of three different healthcare programs provided for "at risk" elderly whereby a new 'hospital based reactivation care program' in the intervention hospital will be compared to the usual care provided in two control hospitals.

### Strengths

First of all, this study uses a mixed methods design of quantitative and qualitative measures that provide information on three elements as stated by Donabedian [87]: structural issues (e.g. materials, personnel, organization and coordination of care), processes (e.g. activities of professional in diagnosing and treating the patient) and patient and caregiver outcomes such as physical functioning and quality of life. According to Donabedian, the combination of these elements allows for better interpretation of findings, as one method may strengthen interpretation in cases where another method cannot explain variances or outcomes. Qualitative data may generate further hypotheses that may be explained by quantitative process and outcome data. It can also provide a context within which outcomes can be explained more in-depth. Secondly, a pilot study was conducted at the intervention hospital before implementing the program, which optimised beforehand the triage for selecting patients to be included in the main study as well as the power calculations and the practical implementation of the main study. Several practical and implementation problems were encountered in the pilot study (e.g. logistics within hospital, personal communication with hospital personnel etc), making it possible to prevent similar problems and sources of bias when conducting the main study. Within the cohort study, dynamic randomisation will be implemented in order to prevent extra bias and missing data per questionnaire. Furthermore, loss to follow up will be minimized by conducting personal interviews through house calls at three months and 12 months after hospital admission. Finally, the evaluation will be conducting a cost-effectiveness study, which will improve/increase current knowledge on the feasibility of implementing transition programs such as the one evaluated here.

### Weaknesses

This study is mainly a cohort study and not a randomised controlled trial (except for the evaluation of a stay at the centre for prevention and reactivation). Nevertheless a cohort study seems our best option for several reasons: Firstly, during hospital treatment, contamination of a control group would be inevitable within one hospital since the same personnel will be treating patients from different groups at the same departments [88]. Secondly, the new program will be the standard care provided in the intervention hospital thereby making randomisation within the hospital not possible. Furthermore, randomisation of treatments between hospitals is not possible since each hospital already has its own standard provided care. Thirdly, during the follow up period after hospital discharge people already have their own regular general practitioner (GP) whose practice is usually close to the patient's home and who is familiar with the patients health and history, making it unrealistic to randomize patients among GP's [88] or home care organizations as well as other first line practitioners. Finally, by conducting a prospective cohort study we aim to investigate health care as provided in a real life situation, thereby improving the generalisability of the study.

Another possible weakness of this study might be the fact that transitions within the three hospitals unrelated to the study may influence outcomes (e.g. at the time of writing this protocol plans exist for starting up specialized clinical geriatric care in the St. Franciscus Gasthuis in light of implementation of national guidelines on elderly care). This may alter differences in levels of health care provided by the hospitals over time thereby influencing outcome and process results. Nevertheless, these changes reflect how health care transitions evolve in real life situations, making the outcomes very valuable nonetheless. They will therefore be monitored closely by means of our quantitative and qualitative process evaluation. To describe the program we will use a methodological approach that combines qualitative and quantitative (mixed) research methods, enabling a thorough and comprehensive evaluation of care for elderly at risk for hospital related functional loss. The introduction of complex, multi component interventions such as this program is sensitive to an array of influences such as details of implementation and context [89,90] and as such calls for embracing a wide range of scientific methodologies. Such a wide range of scientific methodologies helps to obtain information on both mechanisms and contexts, adds to the knowledge on the feasibility and costs of different forms of integrated health care, and highlights the factors that are likely to influence the success and failure of integrated health care for elderly at risk for hospital related functional loss.

### Clinical implications

The results of the study will help determine the most effective way of identifying and treating at risk elderly who are admitted in the hospital in order to prevent unnecessary hospital related functional loss among this group and keep them as independent as possible for as long as possible after they are discharged. In addition, the study may show effective ways to lower the burden of care for primary informal caregivers of elderly patients at risk for functional loss as well as improve their quality of life. Furthermore, the results will increase knowledge on practical issues of implementing a transition in health care and on ways to improve coordination between first and second line care.

